## 5.5.VARIABLES AND EPIDEMIOLOGICAL MEASUREMENTS

Documentation of data at ITM will be pseudonymized, so that missing information could be retrieved by request to the treating physician.

The core “generic” dataset for all selected diseases includes baseline patient characteristics, details on care-seeking trajectories, clinical findings at presentation, diagnostic methods and ascertainment, information on staging, and recommended / administered treatments normally during the whole follow-up period and final clinical/microbiological outcome whenever possible. CRF will be tailored to each specific disease, as the diagnosis and treatment may differ a lot. Due to potential evolving scientific research questions, adjustments of the register/template/dataset might be necessary throughout the study period, in particular if new target disease is identified or new treatments enter clinical practice. Minor adjustments will be collected and notified to the ethics committees; substantial changes will be submitted via an amendment.

The collected data will generically include the following core parameters after anonymization. A disease-specific CRF will be however each time elaborated as all target diseases have important clinical, diagnostic, and therapeutic specificities.

- **General Setup**
  - Epidemiological data on the case: principal investigators name, country, institution, level of care of the institution (e.g., primary care, secondary care)
  - Details on the entered case: Documentation in any other registry (yes/no, if yes DOI), case already published (yes/no)
- **Patient demographics and clinical features at time of diagnosis and initial treatment**
  - Age group, gender, height, weight, associated infections, relevant comorbidities, using Charlson Comorbidity Index (CCI) and in particular immunosuppressive conditions and/or treatments
  - Pre-diagnosis trajectory
  - Clinical signs and symptoms of infection leading to diagnosis and treatment
  - Relevant laboratory parameters (CRP, eosinophilia...)
- **Details on the diagnostic method / case ascertainment**
  - Correspondence to pre-specified case definitions (as composite references standards are often needed for parasitic diseases)
  - Information on disease staging when relevant
  - Details on direct microbiological diagnosis (whenever available)
- **Initial and second line (if any) treatment and outcome**
  - Recommended treatment (in the state-of-the-art section or national guidelines)
  - Administered antiparasitic and adjunctive treatment (in case different of recommended, request to explain the reason for deviation)
  - Description and timing of drug-related adverse event if any

- Need of treatment interruption and reason (availability, adverse event, disease progression...)
- Laboratory changes (Electrolytes, Creatinine, liver function panel, Platelet count, red blood cell count, hemoglobin, white blood cell count, neutrophils, leukocytes, eosinophil count)
- Frequency and timing of follow-up visits with specific findings, if any
- Treatment response regarding clinical features (disease progression vs. stabilization vs. cure), with day of assessment
- Treatment response regarding microbiological outcome: eradication, reduction of the parasitic load, with day of assessment
- If inpatient stay: days on normal ward, intermediate care, intensive care unit total, as a marker of morbidity
- In case of death, cause of death
- Additional information on the case can be entered as a narrative

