| Register Duration   | 
Registry start date: 10/2024
 
Registry end date: none
                                                                                                                                                                                                                                                                                                                                                                                                                                                                                                                                                                                                                                                                                                                                                                                                                                                                                                                                                          |
| Statistical Methods | 
The REDCap database will be analyzed on annual basis to statistically describe different variables as patient demographics, baseline clinical presentation, methods of diagnosis, staging of disease, (recommended) treatments, frequency and pattern of adverse events, complications and clinical outcome. Deviations with suggested treatments will also be captured (as well as reasons for alternative decisions). Association between specific treatment strategies and patient safety/clinical effectiveness will be analyzed using analysis of variance or Student's t-test for the continuous variables (or equivalent non-parametric tests for non-normally distributed variables Mann–Whitney U test or Kruskal-Wallis test) and the chi-square tests or Fisher's exact test for the categorical variables as well as multivariable regressions. Time to event analysis, by using Kaplan-Meier and Cox proportional hazard models will be performed to examine factors associated with specific outcomes.
 |

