#### C. Documentation of clinical course and outcome

- To document the (successive) antimicrobial and adjunctive treatments administered and reasons for any interruption or change
- To observe whether the treatments are administered according to the supervised ITM's state-of-the-art and document the reasons for deviation
- To document the follow-up strategy in the real-life (frequency of visits, monitoring...)
- To determine the proportion of documented microbiological cure, in addition to the defined clinical cure (or stabilization/non-progression)

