As this study is purposed to capture as many cases as possible in all type of clinical settings, and to provide expert advice whenever necessary to colleagues of any discipline (not specialized in tropical diseases), barriers for inclusion will be minimized. Data collection will therefore be retrospective (provided therapy has been initiated since 2022, arbitrarily considered as post-pandemic period). In medical institutions where an opt-out strategy is in place for surveillance or scientific purposes, no formal written inform consent will be required, but inclusion in Tropistry will be presented communicated to the patient, with a notification in the patient file. Data will not be analyzed only if the eligible patient specifically does not consent. In other medical institutions, a written inform consent will need to be signed at whatever moment of the follow-up (with notification in medical file) for the data to be analyzed. Importantly, for every data transfer the entire data file is exported, so that follow-up data of patients can be each time easily incorporated.

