These “recommendations” will of course evolve with the scientific advances and new knowledge (included that generated by Tropistry). It is important to highlight that each center may propose different therapeutic regimens, according to local/national guidelines. As of June 2024, based on the experience at ITM (current state-of-the-art at ITM; manuscript about a recent cluster being submitted), we will recommend in Tropistry the following therapeutic approach:

- In case of symptomatic acute schistosomiasis,
  - If diagnosis earlier than 6 weeks after exposure/infection: only methylprednisolone 0.5 mg/kg/day for 3 days, to be prolonged/repeated if unsatisfactory control of inflammatory symptoms
  - If diagnosis made later than 6 weeks after infection: praziquantel 40 mg/kg single dose, followed after 2-4 hours by methylprednisolone 0.5 mg/kg/day for 3 days, to be prolonged/repeated if unsatisfactory control of inflammatory symptoms (note that this interval allows the concentration peak of praziquantel within 1-2 hours after administration, with no drug interaction)

- In case of asymptomatic acute schistosomiasis (for example within a cluster of cases)
  - Diagnosis earlier than 6 weeks after infection: abstention
  - Diagnosis later than 6 weeks after infection: praziquantel 40 mg/kg single dose followed after 2-4 hours by methylprednisolone (to prevent any clinical exacerbation)

All patients with acute schistosomiasis (either symptomatic or not) will receive a second 40 mg/kg single-dose course of praziquantel at week 12 after infection (to clear all juvenile worms which have meanwhile become adults). Here there is a large consensus between experts.

As already highlighted, the purpose is to make Tropistry as accessible as possible for busy clinicians confronted with any of the target diseases. For pragmatic reasons, inclusion and data entry will be retrospective (with reasonable delay of 6 months after initial diagnosis), and considered as secondary use of clinical data for institutions where an optout strategy is in place. This will be the case with most partners for this first phase of the project focusing on acute schistosomiasis. In other settings, a formal written informed consent will be requested for each included patient.

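### Deviation from recommended treatment has two different comparators: the objective uses the coordinating centre's advice alone, while the data item also accepts a national guideline and so does not request reasons the objective needs

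*Protocol*

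**What the plan says.** Four places in the protocol bear on what counts as a deviation.

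- Section 4.2, part C, sets the objective: "To observe whether the treatments are administered according to the supervised ITM's state-of-the-art and document the reasons for deviation". The comparator is ITM's advice alone.
- Section 5.5 lists the core data item as "Recommended treatment (in the state-of-the-art section or national guidelines"). The next item records the treatment given, with the instruction "in case different of recommended, request to explain the reason for deviation". The comparator is ITM's advice or a national guideline.
- Section 2, under Statistical Methods, says "Deviations with suggested treatments will also be captured (as well as reasons for alternative decisions"). The source of the suggestion is not named.
- Section 8 accepts that "each center may propose different therapeutic regimens, according to local/national guidelines". Section 9 says the same for leishmaniasis.

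Four further statements concern timing. Sections 8 and 9 expect the advice to change as knowledge grows; the only dated version, for acute schistosomiasis, is as of June 2024. Section 5.4 allows data to be entered once the case is complete. Section 7.1 keeps only the year of diagnosis and counts events in days from diagnosis. Section 5.1 admits patients "provided therapy has been initiated since 2022, arbitrarily considered as post-pandemic period", whereas Section 8 gives a delay of 6 months after initial diagnosis for inclusion and entry.

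**The concern.** Sections 4.2C and 5.5 use different comparators for the same question. They agree only when the national guideline and ITM's advice coincide, and the protocol says repeatedly that they may not. Section 8 describes a wide variety of regimens even in specialised settings, and Section 9 describes discrepant guidelines and practice that varies between centres.

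The objective has two parts: whether treatment followed ITM's advice, and why it did not. A site that follows Section 5.5 literally, and treats by a differing national guideline, has no deviation to explain. Its patients then supply nothing to the second part. These are also the patients whose reasons would be most informative, because a recognised alternative was chosen.

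The second strand is the version of the advice. The register has no end date and the advice will change. Advice is shown as short texts at the start of each form section, and a form may be completed long after the treatment decision. The text on screen may then be later than the one the clinician could have seen, and no passage says which version a patient is compared with.

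**Working it through.** The protocol states no adherence or deviation rate, so there is no figure to reproduce. The check is a comparison of the text, followed by two small calculations.

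**Text, patient by patient**

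1. Treated by ITM's advice: no deviation under 4.2C, none under 5.5.
2. Treated by a national guideline that differs from ITM's advice: a deviation under 4.2C, none under 5.5, and no reason requested.
3. Treated by neither: a deviation under both, and a reason requested.

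Only the second group separates the two comparators.

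**Size of the difference (assumed inputs)**

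Let *a* be the share treated by ITM's advice and *g* the share of the remainder treated by a differing national guideline. Neither is in the protocol. Concordance is *a* under 4.2C and *a* + (1 − *a*)*g* under 5.5, so the gap is (1 − *a*)*g*.

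| *a* | *g* = 10% | *g* = 25% | *g* = 50% | *g* = 75% |
|---|---|---|---|---|
| 30% | 7 points | 17.5 | 35 | 52.5 |
| 50% | 5 | 12.5 | 25 | 37.5 |
| 70% | 3 | 7.5 | 15 | 22.5 |

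As a single illustration, take 100 patients, of whom 40 are treated by ITM's advice, 40 by a differing national guideline and 20 by neither. Concordance is 40/100 = 40% under 4.2C and (40 + 40)/100 = 80% under 5.5.

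For scale, Section 5.3 expects at least 100 inclusions per disease. The 95% half-width at 50% is 1.96 × √(0.5 × 0.5/100) = 9.8 points.

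**Version of the advice**

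All events are counted from a day 0 whose calendar date is unknown apart from the year. If the advice changes within a year, a patient diagnosed in that year cannot be placed before or after the change from the register date. The audit trail in Section 5.4 dates data entry, not treatment.

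**Acute schistosomiasis cases at ITM treated before June 2024**

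Section 8 gives about 5 cases a year at ITM.

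- If the 2022 cut-off governs: January 2022 to May 2024 is 29 months, and 29 × 5/12 = 12.1 cases.
- If the 6-month delay is a maximum, a September 2024 start (Section 5.2) reaches back to March 2024: 3 × 5/12 = 1.25 cases. An October 2024 start (Section 2) reaches back to April: 2 × 5/12 = 0.83 cases.

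The range is about 1 to 12, and the protocol does not settle which end applies.

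**The case against.** The strongest reply is that Section 5.5 records the treatment actually given separately from the treatment recommended. An analyst can compare it with ITM's advice however the site read the recommended-treatment item, so the yes-or-no part of the objective need not depend on the site. This largely stands. It does not recover the reasons, which were not requested, or the version in force. Section 5.5 does allow missing information to be sought from the treating physician, but that is a later repair of a gap that the form creates.

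A second reply is that Section 5.5 lists generic parameters only. The full data lists are in annexes that are not shown, and they may record the source of the recommendation. This stands as a limit on the point. The wording of 5.5 would still conflict with 4.2C.

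A third reply concerns dates. A reader might infer that every patient treated from 2022 is scored against the June 2024 advice and is therefore misclassified. The protocol does not support that:

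- No passage says these patients are judged against that text; this would follow only from the absence of a version rule.
- The 6-month delay, if it is a maximum, removes most of them.
- The objective asks whether treatment agreed with the advice, and earlier treatment can agree with later advice, especially at the centre whose experience the advice reflects.
- The June 2024 date belongs to acute schistosomiasis, not to leishmaniasis.

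Finally, the protocol defines no adherence rate, and the shares used above are assumed. At the low end the gap is smaller than the sampling error.

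**Conclusion.** The point holds for the comparator. Sections 4.2C and 5.5 define deviation differently. Followed as written, 5.5 does not request the reasons that 4.2C needs from patients treated by a differing national guideline. The count of deviations varies with the comparator by 3 to 52.5 points over the assumed ranges (*a* from 30% to 70%, *g* from 10% to 75%). Over much of that range this exceeds the 9.8-point half-width. These figures, and the 40% against 80% example, show scale and predict nothing.

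It holds also, more narrowly, for the version: with evolving advice, late entry and only the year of diagnosis, the version in force cannot be assigned from the register within a year of change. The number of ITM schistosomiasis cases that predate the June 2024 advice is about 1 to 12 and depends on how Sections 5.1 and 8 are reconciled.

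The effect is confined to a descriptive secondary objective. The primary objective on safety and clinical effectiveness is not touched. The finding is that the comparator and its version should be fixed in the data capture. It takes no view on which treatment advice is right.

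**What to change.** Replace the recommended-treatment item in Section 5.5 with two items.

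1. Concordant with the Tropistry/ITM recommendation: yes or no, with the version in force at treatment start, or none in force.
2. Concordant with a national or local guideline: yes, no, or none exists.

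Request a reason whenever item 1 is no, including when item 2 is yes. State in Section 5.6 that objective 4.2C is reported from item 1 and that item 2 is reported beside it. Use the same term for the comparator in Sections 2, 4.2C and 5.5.

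Have the site choose the version when it enters the case, since it knows the treatment date; the register then needs no calendar date and Section 7.1 is unaffected. Report patients treated before any version was in force as a separate stratum, for concordance only, rather than dropping them. Reconcile the 2022 cut-off in Section 5.1 with the 6-month delay in Section 8, so that the size of that stratum is known.

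The cost is one or two extra form fields, a version label on each advice text and a sentence in Section 5.6. Sites are not paid per case and the register aims to keep barriers low, so the added burden is real but small. If the annexes already record the source and version, only the wording of Section 5.5 and the trigger for the reason need to change.

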## 4. OBJECTIVES

### 4.1. PRIMARY OBJECTIVE

To document the **safety** (frequency and pattern of adverse events) and **clinical effectiveness** (cure or stabilization rate at relevant timepoint) of current treatments for patients diagnosed with any of the selected tropical diseases (listed below\*) in Belgian and European hospitals and travel clinics.

1. Acute schistosomiasis
2. Neurocysticercosis
3. Chagas disease
4. Cystic echinococcosis
5. Cutaneous leishmaniasis

\*This selection is indicative and limited to parasitic diseases, based on the considerations described in the text, and may evolve according to the needs. Also, the extension of the registry to each disease will be progressively phased, following the proposed order.

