## 5. METHODOLOGY

### 5.1. REGISTER DESIGN

For this national and international multicentric effort, REDCap (Research Electronic Data Capture) will be used to offer harmonized disease-specific case report form (CRF), as well as state-of-the-art recommendations. REDCap is a GCP-compliant web-based metadata open-source software program available to academic institutional partners of Vanderbilt University. It protects data with secure web authentication, data logging and Secure Sockets Layer (SSL) encryption, and has features specifically designed for registry data management, including (i) customizable data collection forms, (ii) data validation and quality control checks, (iii) advanced reporting and export capabilities and iv) audit trails for tracking changes to data.

The Tropistry REDCap-based registers (one for each selected tropical disease) are being constructed to collect relevant demographic, diagnostic and clinical data using a predefined core dataset (Section 6.5 for full details). It is designed as a registry to harmonize as much as possible the selection of treatments (based on state-of-the-art review and expert advice) and suggested follow-up. Recruitment will include all patients diagnosed with one of the target diseases (see case definitions for each of them), either a treatment has to be initiated or not. Data will be entered directly into REDCap by an investigator from each participating site. Data will be stored pseudonymously at ITM.

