The treatment of acute schistosomiasis, either symptomatic (Katayama syndrome) or not, is even more challenging than its diagnosis. As the symptoms are mainly driven by the hypersensitivity reaction, corticosteroids need to be administered in diseased patients, but the optimal timing, dosage and duration are poorly established in the absence of randomized trials. It makes sense to associate the (currently unique) antischistosomal drug, praziquantel, to kill off the already matured schistosomes, but this treatment is largely ineffective against juvenile worms, partly responsible of the symptoms. Therefore, most of the time experts do not recommend praziquantel in the early phase of the acute infection, arbitrarily established within 6 weeks after infection, while it should/could be administered later on. But here again and for the same reason, the optimal timing and dosage of praziquantel to completely clear the infection are unknown, and many different regimens are in place according to local experience and expert-based guidelines. In addition, the interactions between corticosteroids and praziquantel are poorly understood but it appears that the blood concentration of the latter drug substantially decreases when co-administered with corticosteroids. Finally, the administration of praziquantel in asymptomatic, or mildly symptomatic, infected individuals may provoke in more than 50% of cases a serious clinical exacerbation (by antigenic release). Overall, there is no evidence regarding the optimal therapy of acute schistosomiasis, and a wide variety of regimens are proposed

even in specialized setting, as highlighted in 2019 by a survey of the European network of travel clinics, TropNet (unpublished data).

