| Mucosal involvement        | Yes                                                         | Yes                                             | Yes                                              |
| Immunosuppression          | Yes                                                         | Yes                                             | Yes                                              |
| Failure to local treatment | Yes                                                         | Yes                                             | Yes                                              |
| DCL/LR                     | Yes                                                         | Unclear                                         | Yes                                              |

|                      |         |         |         |
|----------------------|---------|---------|---------|
| Subcutaneous nodules | Yes     | Unclear | Yes     |
| Lymphatic spread     | Yes     | Yes     | Yes     |
| Infection in Bolivia | Unclear | Yes     | Unclear |

DCL: diffuse cutaneous leishmaniasis, LR: Leishmania recidivans

aFor the IDSA guidelines there are cases where the simple and complex is not mutually exclusive; e.g. 1-4 cm size, and 2-4 lesions

bA distinction is made between Old-World species (with the addition of *L. mexicana* from the New-World), for which more than 3 lesions are considered to be complex, while for New-World species (with the exception of *L. mexicana*) having multiple lesions is sufficient to qualify as complex cutaneous leishmaniasis.

In general, for simple CL, observation/simple wound care or local treatment are sufficient, while systemic therapy should be considered for complex CL. Of note there are still slight differences between guidelines about some criteria (especially regarding the size and number of lesions) but treatment decisions based on "common sense" will be suggested whenever discrepancies occur. In all cases, confirmation of the diagnosis is important, and whenever feasible, PCR-based species identification will be recommended because it increasingly guides therapy choices. However, species typing might not be available everywhere; in such cases, clinical judgment and knowledge of the probable region of infection will guide management.

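### The only adverse-event item in the core dataset is limited to drug-related events: it is narrower than the primary safety objective and empty for any drug-free period

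*Protocol*

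**What the plan says.** Section 4.1 gives safety and clinical effectiveness as the two parts of the primary objective and defines safety as "frequency and pattern of adverse events" of current treatments. Section 5.6 plans tests and regressions of the association between treatment strategies and patient safety.

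The generic core list in section 5.5 has one item that describes and times adverse events: "Description and timing of drug-related adverse event if any". The same list also asks, without any causality limit, for laboratory changes, findings at follow-up visits, clinical response (progression, stabilization or cure), ward and intensive-care days, cause of death and a free narrative. Adverse event also appears as a possible reason for interrupting treatment.

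On who is in the register, section 5.1 recruits all diagnosed patients, "either a treatment has to be initiated or not", but then limits retrospective collection to cases "provided therapy has been initiated since 2022". Strategies without drug are named in both disease modules. In section 8, for asymptomatic acute schistosomiasis: "Diagnosis earlier than 6 weeks after infection: abstention". In section 9: "for simple CL, observation/simple wound care or local treatment are sufficient". Section 8 adds that all acute schistosomiasis patients "will receive a second 40 mg/kg single-dose course of praziquantel at week 12 after infection".

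On the expected safety event, the section 8 background says that praziquantel in asymptomatic or mildly symptomatic infected people "may provoke in more than 50% of cases a serious clinical exacerbation (by antigenic release". It also says that the symptoms of the disease itself come mainly from a hypersensitivity reaction.

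**The concern.** An adverse-event frequency should be countable in the same way under every strategy that is compared. An item that opens only once the treating doctor has judged an event drug-related does not allow that, for two reasons.

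First, a patient without drug cannot have an entry during that time, whatever happens clinically. Second, the judgement is made by someone who knows the treatment, and the text shown gives no stated criteria. For the event that matters most in the first module, a flare after praziquantel, the alternative label of disease activity is plausible because the protocol describes both as immune-driven. Recorded rates could then differ between centres or regimens through attribution habit and not through safety.

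A statistical analysis plan could not repair this. An event judged unrelated and never entered leaves no gap to query, and the register has no end date.

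**Working it through.** The protocol gives no sample size calculation, power or event count, so there is no figure to reproduce. The check compares the passages and adds two illustrations under stated assumptions.

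**1. Objective against data item**

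| Element | Section | Content |
|---|---|---|
| Primary safety measure | 4.1 | adverse events, no causality limit in the definition |
| Core adverse-event item | 5.5 | drug-related events only |
| Causality criteria or adjudication | text shown | none |
| Patients enrolled | 5.1 | treated or not, in tension with the therapy-since-2022 condition |
| Strategies without drug | 8, 9 | abstention before week 6; observation or wound care |
| Use | 5.6 | strategies compared on safety |

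The item is narrower than the definition, and the planned comparison can include strategies for which the item is empty.

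**2. How far the empty field reaches**

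- Cutaneous leishmaniasis under observation or wound care: empty for as long as no drug is given.
- Schistosomiasis abstention: empty until praziquantel is given. Under the section 8 approach that is by week 12, so the field is not empty over the whole follow-up.
- The number of never-treated patients cannot be determined, because the two conditions in section 5.1 pull in different directions.

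**3. Dependence on attribution**

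Recorded rate = true rate × share of events that the doctor attributes to the drug. The true rate is set at 50%, the floor of the section 8 figure, which applies to asymptomatic or mildly symptomatic patients only. The attribution shares are assumed.

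| Share attributed | Recorded rate |
|---|---|
| 100% | 0.50 × 1.00 = 50% |
| 75% | 0.50 × 0.75 = 37.5% |
| 50% | 0.50 × 0.50 = 25% |
| 25% | 0.50 × 0.25 = 12.5% |

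**4. What a drug versus no-drug comparison on this item could show**

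Assumptions: the 100 expected inclusions split 50 and 50, the same true all-cause event rate in both groups, and a two-sided level of 0.05. With 0 of 50 recorded in the no-drug group, Fisher's exact p for k of 50 in the drug group is 2·C(50,k)/C(100,k). This gives 0.056 for k = 5 and 0.027 for k = 6, so six recorded events suffice. The chance of a significant result is P(X ≥ 6) with X binomial (50, recorded rate):

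| True rate, both groups | All attributed in drug group | Half attributed |
|---|---|---|
| 10% | recorded 10%: 38% | recorded 5%: 4% |
| 20% | recorded 20%: 95% | recorded 10%: 38% |
| 30% | recorded 30%: over 99% | recorded 15%: 78% |

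The true difference is zero in every cell. These figures show the mechanism; they do not forecast the register's results.

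**5. Do the unattributed fields compensate?**

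In part. They cover untreated patients too, apart from the interruption item. But a flare that resolves can end as cure in the response field. Section 8 says acute patients only exceptionally need hospital care. Interruption hardly applies to a single-dose drug. Laboratory values do not code a clinical flare. Visit findings and narrative are unstructured. A severe event would probably leave a trace, but none of these fields gives an adverse-event frequency that can be compared between strategies.

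**The case against.** The strongest reply is that the objective concerns the safety of treatments, and that the summary in section 2 speaks of events related to them. On that reading a drug-related item fits, and zero for an undrugged patient is a true value. This is a fair reading of intent. It does not say who judges relatedness or by what criteria, and it does not make the count usable for comparing a drug strategy with a no-drug one.

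Second, section 5.5 is only the generic core. The disease-specific lists are in Annexes 2 and 4, which are not in the text at hand and may already record all events or exacerbations. This stands and confines the point to section 5.5.

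Third, attribution may work better than feared. A new flare in an asymptomatic patient soon after praziquantel is the easier case, and the protocol itself ascribes it to the drug. The first sites are university travel clinics, entry after each visit is recommended, and expert advice is available. These points make low attribution shares less likely. However, section 5.4 also allows entry once the case is completed, and section 5.1 aims at clinicians of any discipline.

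Fourth, a reader might infer that the register holds no safety data beyond drug-related events, or that untreated strategies score zero whatever happens. The documents support neither: the unattributed fields exist, and abstention patients are due praziquantel at week 12. Nor can treated-versus-untreated comparisons be called invalid as planned, because section 5.6 speaks of strategies in general and names no such contrast.

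**Conclusion.** The point holds for the generic core dataset. Its only adverse-event item needs a drug-related judgement without stated criteria, while the primary safety measure is defined without that limit and strategies, some without drug, are to be compared on safety. The item is empty for drug-free periods: before praziquantel in the abstention group, and throughout observation or wound care in cutaneous leishmaniasis.

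The size depends on attribution, which the protocol does not give. At a true exacerbation rate of 50%, shares of 25% to 100% move the recorded rate from 12.5% to 50%. That is a fourfold range produced by labelling alone, and it applies to asymptomatic or mildly symptomatic patients only. The range shows sensitivity; it is not evidence that centres differ this much.

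This should be fixed. The unattributed fields, the week-12 treatment and the unseen annexes keep it from being a defect that defeats the safety objective outright.

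**What to change.** In section 5.5, reword the item to *any new or worsening clinical event after day 0, regardless of suspected cause*. Record for each event the onset day relative to each treatment, seriousness, and a separate causality field with stated criteria. Add a yes/no item for clinical exacerbation after praziquantel that asks for no attribution. Check both against Annexes 2 and 4. If an annex already records more, align the core wording with it. Reconcile the two statements in section 5.1 on whether patients without therapy are included.

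Report all-cause events alongside drug-related events, and do not compare no-drug with drug strategies on the drug-related count alone. A compulsory all-cause measure in a fixed window is harder to justify here, because visits follow routine practice and untreated patients' notes may not support it.

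The cost is a few more fields per case in a register that pays no case fees, and higher raw event counts that will include disease symptoms. No treatment or visit changes.
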